## Abstract

**Background/Objectives**: Clinical childbirth in high-income countries is increasingly shaped by standardised routines that do not always accommodate individual preferences. In Germany, approximately one in eight pregnant persons experiences clinically significant childbirth-related post-traumatic stress disorder symptoms, with pregnant persons facing language or health-literacy barriers being at particular risk of inadequate preference integration. **Methods**: This paper presents the conceptual foundation and proposed study design for FAIR-Birth, an interdisciplinary initiative to develop and feasibility-test a mobile application supporting Advance Birth Planning (ABP) embedded within midwifery-led antenatal care. The intervention combines four elements: transfer of the Advance Care Planning concept to antenatal care, a domain-restricted Large Language Model (LLM) supporting multilingual preference articulation, integration of the resulting ABP document into midwifery-led continuity of care, and iterative adaptation. Following the updated MRC framework, this study will employ a sequential mixed-methods design encompassing systematic review, participatory instrument development, Delphi consensus on the knowledge base, iterative technical development with usability testing, and a feasibility study across two perinatal centres in Bavaria. **Results/Conclusions**: FAIR-Birth is expected to generate a content-validated ABP instrument, a domain-restricted multilingual LLM dialogue system, and an evaluated application prototype. The work corresponds to the development and feasibility phases of the MRC framework; effectiveness questions are reserved for a planned subsequent randomised controlled trial.

## 1. Introduction

Clinical childbirth in high-income countries is increasingly shaped by standardised routines that do not always accommodate individual needs. In Germany, more than 690,000 births occurred in 2023; 98% took place in clinical settings, frequently attended by previously unknown obstetric staff [1,2]. Limmer and colleagues, in a sample purposively recruited for high exposure to disrespectful care, reported obstetric interventions performed without full informed consent in up to 43% of hospital births [3]. Approximately one in eight pregnant persons experiences clinically significant childbirth-related post-traumatic stress disorder (CB-PTSD) symptoms, with full CB-PTSD developing in between 4% and 12.5% of cases, depending on the measurement approach [4,5]. Associated effects include impaired mother-infant bonding, breastfeeding difficulties, and strained partnerships [4].

Evidence on preference integration in birth care points in a consistent direction: integrating the birthing person’s preferences into the birth process is associated with higher satisfaction, fewer unnecessary interventions, and improved birth experience [6,7,8]. Midwifery-led continuity-of-care models are associated with lower caesarean section rates and improved maternal outcomes [9].

Birth plans are an established but imperfect instrument for the purpose of preference articulation. A systematic integrative review found that while birth plans can increase discussion of preferences with care providers, they are frequently too static and too detailed to accommodate the dynamic nature of labour [10]. Existing digital tools focus predominantly on the care provider’s side of the encounter [11]. Several existing approaches address parts of this gap. The Birth Map is a structured, yet user-oriented and flexible, woman-led birth-preparation tool in book format, empirically evaluated in an Australian context, but it is English-only, static in format, and not integrated into the clinical record [12]. CHAT-maternity-care [11] addresses the care-provider side, supporting providers in assessing parents’ health literacy rather than supporting pregnant persons in articulating preferences. Conversational agents for perinatal health are an emerging field [13,14,15], with no instrument to date specifically structured around antenatal preference articulation. General-purpose LLMs are accessible but not domain-restricted; without grounding in validated content, their obstetric output risks being inaccurate or misread as clinical guidance [14]. FAIR-Birth is designed to bring these elements together—structured preference articulation on the pregnant-person side, digital adaptivity, multilingual access, and integration into midwifery-led continuity of care—within a single instrument.

Communication barriers compound this gap. Approximately 13.4% of the German population did not grow up speaking German as a first language [16]. Pregnant persons with migration history and limited German proficiency face elevated risks of inadequate informed consent and loss of autonomy during labour [17]. Midwifery students in Germany receive limited standardised training in the care of pregnant persons with language barriers, FGM/C (Female Genital Mutilation/Cutting), or experiences of racism—a curricular gap that may reinforce existing inequalities in clinical practice [18].

Digital health technologies offer an opportunity here. Conversational agents based on LLMs can deliver information and support shared decision-making at scale, adapting to a user’s language and health-literacy level [19]. What is missing is not digitalisation alone but a dynamic, adaptive instrument responsive to a pregnant person’s evolving preferences across successive encounters, which a domain-restricted LLM is suited to provide.

This paper presents the conceptual foundation and proposed study design for FAIR-Birth (Fair, AI-supported, Informed, Respectful), an interdisciplinary research initiative to develop and feasibility-test the FAIR-Birth intervention: a mobile application supporting Advance Birth Planning (ABP) embedded within midwifery-led antenatal care. The FAIR-Birth intervention combines four elements: the transfer of the Advance Care Planning (ACP) concept to the antenatal context; the use of a domain-restricted Large Language Model to support multilingual preference articulation; integration of the resulting ABP document into midwifery-led continuity of care; and iterative adaptation of preferences across antenatal encounters. Each component has precedents in the literature on ACP, on digital decision support in maternity care, and on midwifery-led care models. Because these four elements have previously only been evaluated in isolation, the primary contribution of FAIR-Birth lies in their operational integration within a unified, midwifery-led antenatal care workflow.

The acronym FAIR refers to the procedural equity principles underlying the project: that clinical birth should be transparent, participatory, and responsive to individual preferences regardless of linguistic or social background. Whether the FAIR-Birth intervention may produce equitable outcomes is a question for the planned trial.

This paper presents the protocol prior to formal funding and ethics approval. Both will be obtained before data collection commences. Publishing at this stage invites methodological scrutiny and establishes conceptual transparency before the intervention is built. The relationship of the study to the phases of the MRC framework for complex interventions is set out in Section 4.1.

The remainder of the paper is structured as follows: Section 2 develops the theoretical framework; Section 3 describes the FAIR-Birth intervention concept; Section 4 outlines the proposed methodology; and Section 5 discusses possible implications and limitations.

## 2. Theoretical Framework

### 2.1. From Advance Care Planning to Advance Birth Planning

Advance Care Planning (ACP) is a structured process through which individuals clarify, document, and communicate their values, goals, and preferences regarding future medical care, in dialogue with healthcare professionals and significant others [20]. Evidence indicates that ACP can improve concordance between patients’ expressed wishes and the care they receive, reduce decisional conflict, and increase satisfaction among patients, families, and care providers [21,22,23].

Transferring the ACP concept to childbirth is conceptually motivated and practically supported. Childbirth shares structural conditions with end-of-life care—high relevance for the individual, physiological intensity, time pressure, and an often-unfamiliar care team [3,10]—that constrain real-time deliberative decision-making. Documented preferences expressed in advance can be carried into encounters where the deliberation would otherwise occur under time pressure [24].

The analogy is, however, partial. ACP responds to anticipated cognitive or medical incapacity in life-limiting illness. ABP addresses the temporary erosion of deliberative space during a physiologically normal process. The pregnant person retains full legal decision-making capacity throughout; what is at risk is the practical conditions for its exercise under pain, urgency, and institutional power of the clinical team. ABP is therefore not a transfer of substituted-judgement logic but of the dialogic structure of ACP adapted to the antenatal setting.

A precedent procedure exists in perinatal palliative care, where Garten et al. extended ACP into a structured, prospective, revisable prenatal planning process for pregnancies affected by life-limiting foetal conditions [25]. FAIR-Birth draws on the same dialogic and documentary structure, but differs in two respects: it addresses physiologically normal birth, and it centres on the competent pregnant person’s own preferences rather than anticipatory decision-making by parents on behalf of a child.

ABP adapts the dialogic structure of ACP to the antenatal routine context. It focuses on values and preferences regarding birth, rather than incapacity scenarios. Its output is a structured articulation of preferences rather than a static birth plan. Preferences are revised iteratively across antenatal encounters. The process is integrated into midwifery-led continuity-of-care, the relational context ACP research identifies as central to the concept’s effects [23].

### 2.2. Shared Decision-Making in Midwifery-Led Intrapartum Care

Shared decision-making (SDM), the joint process by which patients and healthcare professionals participate in clinical decisions, has become a normative standard in healthcare policy [26,27,28]. The 2020 German S3 guideline on physiological vaginal birth at due date explicitly calls for integrating women’s perspectives into clinical decision-making [29]. In obstetrics, SDM faces practical barriers: decisions are often required rapidly, under physical and emotional intensity, within a care relationship that may have formed only moments before [30].

ABP relocates the deliberative phase of SDM to the antenatal period, where the pregnant person has the time and cognitive space for structured reflection. The counselling midwife acts as a facilitator rather than a decision-maker. The ABP document may then provide an SDM infrastructure that persists across encounters, refined at successive antenatal appointments, stored in the electronic patient record (TI-ePA), and retrieved by the clinical team at birth. The FAIR-Birth application thus functions as a preparation and communication infrastructure.

### 2.3. Health Equity and the FAIR Framework

The third theoretical pillar of FAIR-Birth is health equity, understood procedurally. Procedural equity concerns whether each pregnant person has genuine access to the informational and deliberative resources required to exercise autonomous choice—not whether outcomes are equal across groups. Drawing on Rawlsian fairness [31,32], fairness of a care encounter depends not on whether the same procedure was offered to everyone but whether each pregnant person could reflect on, articulate, and communicate their preferences.

This procedural framing has empirical correlates that a feasibility study can examine, even if outcome-level equity cannot yet be tested. Knowledge of healthcare rights and perception of available resources during pregnancy and birth are unequally distributed, particularly among pregnant persons with undesired pregnancies [33]. Those with limited health literacy are underserved by existing birth plan formats [10] and those with migration history face language and system unfamiliarity [17].

FAIR-Birth operationalises procedural equity through three design choices. Firstly, the ABP instrument and application are multilingual by design, supported by an LLM adapting to the user’s language and health literacy level [34,35]. Secondly, the information component follows standards for evidence-based health communication [36,37]. Thirdly, the participatory development process involves pregnant persons, midwives, and clinical partners as co-designers [38].

Whether these choices produce more equitable outcomes is a question for the planned trial. The feasibility study examines whether the equity-supporting infrastructure can be implemented and used.

A positive birth experience is defined less by the absence of intervention than by the degree to which a pregnant person feels heard, informed, and in control [6,39], the conditions FAIR-Birth is designed to support.

## 3. The FAIR-Birth Intervention Concept

### 3.1. The Advance Birth Planning Instrument

The ABP instrument is the core preference-articulation component of the FAIR-Birth intervention. It is a structured, self-reflective dialogue guide that leads pregnant persons through a staged process of identifying, articulating, and documenting their preferences and goals for clinical birth. The process is organised into six domains, addressed sequentially and presented in Figure 1.

The six-domain architecture, adapted from [25], reflects the iterative and non-linear nature of antenatal preference formation. Birth preferences are not fixed at the outset of pregnancy; they emerge through dialogue, information, and self-reflection over time [40]. The ABP instrument is therefore a structured framework for an ongoing reflective process rather than a one-time exercise. It produces an ABP document recording current preferences and the conditions under which specific interventions would be acceptable, revised as preferences develop.

The ABP instrument complements existing care-provider-side tools by addressing the pregnant person’s side of the same encounter, equipping the pregnant person to articulate and communicate their own preferences. Together, the tools may support shared decision-making by giving both parties structured preparation for the antenatal dialogue within a midwifery-led care model.

### 3.2. The FAIR-Birth Application: LLM Architecture and Knowledge Infrastructure

The FAIR-Birth system will deliver the ABP instrument digitally and make evidence-based information about obstetric interventions accessible in a personalised, multilingual, and dialogically adaptive format.

Instrument development will follow an iterative participatory process. Focus groups with pregnant persons, practising midwives, and obstetric clinicians will generate design principles and content requirements. Cross-cultural validation across languages is planned to follow established methodological COSMIN standards [41,42]. The application’s information architecture will rest on a curated multilingual knowledge base covering common obstetric interventions (induction of labour, pain management, episiotomy, and caesarean section), as presented in Figure 2, developed through a systematic literature review and structured evidence synthesis and validated through a Delphi consensus process. Information follows established standards for evidence-based health communication, including evidence fact boxes [37] and the German guideline for evidence-based health information [36]. An LLM makes this knowledge base dynamically accessible. A core design choice is that the LLM does not generate clinical recommendations. Its function will merely be to facilitate the identification and structured articulation of individual preferences by presenting relevant information in the user’s preferred language at an appropriate health literacy level and guiding the reflective dialogue that produces the ABP document. FAIR-Birth is intended to serve as a preference elicitation and communication tool, not a clinical decision support system. This design choice shall address a core limitation of general-purpose LLMs in obstetric contexts. Without domain restriction, models such as ChatGPT 5.5 risk generating inaccurate, incomplete, or contextually inappropriate responses and may be misread by users as clinical guidance [14]. The FAIR-Birth system is designed to mitigate this through its curated knowledge base and Retrieval Augmented Generation (RAG) architecture, which may confine the model’s output to validated content. For direct clinical queries, the system employs a multi-layered risk-mitigation strategy. A guardrail classifier intercepts requests for clinical advice before retrieval; rather than generating a recommendation, the system redirects the query to the relevant evidence fact box, prompts reflection on the user’s own values, and records it in the ABP document for discussion with the midwife. Substantive clinical questions are thus routed to a qualified professional while the system continues to support structured preference articulation. Figure 2 gives an overview of the system architecture.

The LLM integration will follow a staged, non-fine-tuning adaptation strategy. Initial deployment shall employ RAG [43], in which the model queries a vector database of validated content prior to response generation, preventing output beyond the knowledge base. Task-specific behaviour is refined through advanced RAG techniques (query transformation, re-ranking), iterative system-prompt adaptation, few-shot prompting, and inference-time steering vectors [44,45]. In-context and test-time interventions require no participant interaction data for training. Reinforcement learning from human feedback and parameter-efficient fine-tuning are deferred to the subsequent randomised controlled trial, where a larger dataset and a dedicated consent process can be designed. The LLM component will be subject to continuous quality monitoring throughout the project period, comprising the instruction-following rate (accuracy), human-preferences alignment scores, and refusal rates under adversarial conditions. Full behavioural validation of the system across sites is a development-phase activity feeding the planned randomised controlled trial, rather than a confirmatory exercise completed within this protocol.

To provide an operational overview of the system’s technical boundaries, key implementation decisions, safety guardrails, and quality tracking metrics are structured in Table 1.

Transparency, explainability, and privacy are embedded in the system architecture from inception [46]. The FAIR-Birth application is being designed to meet the requirements applying to AI in healthcare through documented system behaviour, continuous performance monitoring, and expert-validated content.

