### 3.3. Embedding FAIR-Birth in Midwifery-Led Antenatal Care

The FAIR-Birth intervention is not designed as a standalone person-facing technology. It is an ABP instrument and an ABP document, delivered through the FAIR-Birth application, embedded within midwifery-led antenatal care. The midwife’s contribution will be central to the intervention: the midwife has to introduce the ABP process at an antenatal appointment, facilitate discussion of the developing ABP document at subsequent appointments, and support its integration into the clinical record. This model is consistent with evidence on the effectiveness of midwife-led continuity of care [9] and with the broader move toward person-centred, relationship-based perinatal care [47].

Once completed and discussed, the ABP document is stored in the electronic patient record (TI-ePA) and available to the clinical team at birth. It gives the birthing person’s prior-articulated preferences a route into a care encounter where the team is otherwise meeting them for the first time [12].

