### 4.3. Phase 2: Feasibility Study (Months 19–30)

A prospective, mixed-methods feasibility study will be conducted with the developed ABP instrument across two perinatal centres in Bavaria. The study will follow a sequential explanatory mixed-methods design [60]. Quantitative feasibility data will be collected first and subsequently elaborated through qualitative inquiry.

Setting and participants

Two level I/II perinatal centres in Upper Bavaria (approximately 1500–3000 births per year) have been identified as study sites. Eligible participants are pregnant persons in their second or third trimester in routine antenatal care; purposive sampling will ensure representation across migration history and health literacy. A target sample of n = 30–50 is planned. As this is a feasibility study, no power calculation is required; sample size is justified by the study’s objectives—estimating recruitment rates, assessing acceptability, and identifying procedural uncertainties for the planned trial [61].

Quantitative feasibility outcomes

Quantitative feasibility data will be collected across four domains: recruitment (proportion of eligible and approached pregnant persons who consent; retention over the antenatal period), engagement with the FAIR-Birth application (completion of the ABP process; time spent in each ABP stage), procedural feasibility (data completeness; technical errors; midwife workload), and acceptability (Mobile App Rating Scale [MARS] [59] scores from pregnant persons and midwives). The four feasibility domains above (recruitment, engagement, procedural feasibility, and acceptability) constitute the primary feasibility signals informing the progression decision. The pilot psychometric measures introduced below are explicitly subordinate to a parameter-estimation role: they are collected to estimate variance and the plausible range of effect sizes for the future randomised controlled trial sample-size calculation, and are expressly not used to test effectiveness.

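### The handling stated for intercepted clinical questions suits choices about interventions but not a message about a current symptom, and no shown text tells that user to seek care

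*Protocol article*

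**What the plan says.** Section 3.2 of the protocol article limits the role of the language model: "FAIR-Birth is intended to serve as a preference elicitation and communication tool, not a clinical decision support system". For direct clinical queries it describes a risk-mitigation strategy with several layers. "A guardrail classifier intercepts requests for clinical advice before retrieval". After interception no recommendation is generated; instead "the system redirects the query to the relevant evidence fact box, prompts reflection on the user’s own values, and records it in the ABP document", so that it can be discussed with the midwife. The section concludes: "Substantive clinical questions are thus routed to a qualified professional while the system continues to support structured preference articulation".

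The knowledge base behind the fact boxes is described as "covering common obstetric interventions (induction of labour, pain management, episiotomy, and caesarean section". Section 3.3 says that the midwife will "facilitate discussion of the developing ABP document at subsequent appointments". Table 1 repeats the guardrail in brief: the classifier intercepts, and clinical questions are redirected to fact boxes and to midwives. Quality monitoring is described as "comprising the instruction-following rate (accuracy), human-preferences alignment scores, and refusal rates under adversarial conditions".

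On who will use the app in Phase 2, Section 4.3 states: "Eligible participants are pregnant persons in their second or third trimester in routine antenatal care". The planned sample is 30 to 50.

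**The concern.** The authors expect users to put clinical questions to the app, which is why the guardrail exists. The response they describe was designed for a person weighing up an intervention: read balanced information, think about your values, take the question to your midwife. A person in later pregnancy who types a message about something she is feeling now needs a different response, namely to be told that the app cannot help and that she should contact someone who can.

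At stake is the safety of a small number of participants in Phase 2. The article leaves full validation of the model's behaviour to the later randomised trial (Sections 3.2 and 5), so these participants use the app before that work is complete. Section 2.3 notes that people with a migration history may be unfamiliar with the language and the health system. A clear instruction in the user's own language therefore matters most for the group the project aims to reach.

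**Working it through.** The plan gives no figure to reproduce, and the point depends on no sample-size input. The check sets the stated steps side by side and follows two kinds of message through them.

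**Stated steps**

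| Step | What the article states | Where |
|---|---|---|
| Trigger | Requests for clinical advice, with no split by urgency | Section 3.2 |
| Response | Fact box, values prompt, entry in the ABP document | Section 3.2 |
| Hand-off | Follows from the ABP entry; no alert or time limit given | Section 3.2 |
| Discussion of the ABP document | At later appointments, as part of the midwife's general role | Section 3.3 |
| Topics available | Induction, pain management, episiotomy, caesarean section | Section 3.2 |
| Out-of-scope requests | Refusal rate is tracked; wording of a refusal not given | Table 1 |

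**Message A: should I accept an induction?** It is intercepted, a relevant fact box exists, a values prompt is apt, and discussion at an appointment is appropriate. The route works.

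**Message B: a symptom present now.** The shown text allows three paths.

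1. *Intercepted as a request for advice.* Of the four named topics, four are interventions and none is a symptom or warning sign, so no named topic supplies a relevant fact box. A values prompt has nothing to act on. The entry waits for the midwife, and the only timing in the text is that in Section 3.3.
2. *Refused as out of scope.* Table 1 tracks how often this happens, but neither it nor Section 3.2 says what the user then reads.
3. *Missed by the classifier.* The retrieval design is meant to keep output within the knowledge base, and none of the named topics would supply advice to seek care.

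On none of the three does a shown sentence tell the user to contact a clinic, a midwife or the emergency services.

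**Would Phase 2 notice?** Three monitoring metrics are listed: instruction following, preference alignment and adversarial refusal. One of the three sits in the guardrail-classifier row of Table 1, and it measures whether interception occurred. The procedural-feasibility domain in Section 4.3 covers completeness of data, technical faults and the workload of midwives. A symptom message intercepted as designed is not a technical fault, so none of these items would record it. The interviews may touch on the subject but do not count it.

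**The case against.** The strongest case against is that this is largely a matter of missing detail. The article condenses a fuller plan, was published before funding and ethics approval, and describes an app that is not yet built. The wording of safety messages would normally sit in a technical specification. Section 4.1 assigns questions about the app's legitimate scope to the workstreams, clinicians and midwives contribute content requirements, and usability rounds precede Phase 2. A suitable response could well be added there.

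Much of this stands, and it limits the size of the point. It does not remove it, because Section 3.2 states an actual handling rule, and that rule serves the symptom case badly. None of the planned steps commits to a different response.

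A reader might infer three stronger claims, which the documents do not support:

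- *That every clinical request must take this one route.* The strategy is said to have several layers, Figure 2 cannot be checked, and a symptom message might be refused as out of scope. The reference to a relevant fact box and to the user's values also suggests that the authors had intervention questions in mind.
- *That a symptom message would be held until the next appointment, with a calculable delay.* Section 3.2 gives no timing, and Section 3.3 describes the midwife's general work with the document. The article gives no visit interval and no rate of symptom messages, so a delay figure would reflect only the reviewer's assumptions. Nothing prevents a user from telephoning her clinic directly.
- *That the app needs an urgency classifier.* Sorting messages into urgent and non-urgent is itself a triage judgement. It would need testing in each language and sits uneasily with the stated scope. A fixed message shown regardless of content avoids this.

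**Conclusion.** The point holds as a cheap patient-safety improvement of minor severity. As described, the only handling stated for intercepted clinical requests suits questions about interventions and not a message about a current symptom. If such a message is refused instead, the response is not stated. The article does not contradict itself here, and the point does not show that the app would be unsafe.

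Its size can be given only in the plan's own terms: none of the four named topics fits, the one metric placed against the guardrail classifier measures interception, and 30 to 50 participants are planned. How often symptom messages would occur is unknown.

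The conclusion assumes that Section 3.2 and Table 1 reflect the intended design, that Figure 2 does not add a separate branch, and that a pregnant user of a conversational app may at some time write about a symptom. If Figure 2 or a fuller specification already contains a response that directs the user to care, only the wording of the article needs attention.

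**What to change.** 1. In Section 3.2 and Table 1, state that the app does not handle symptoms.
2. Add one fixed message, approved in each app language before Phase 2, shown permanently on the chat screen and in every guardrail intercept or refusal. For example: *This app cannot assess symptoms. If you have a symptom or are worried now, contact your clinic or midwife; in an emergency call the emergency services.*
3. Limit the Section 3.2 statement that clinical questions reach a professional to non-urgent questions.
4. Under procedural feasibility in Section 4.3, report the number of intercepted queries from the app logs.

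A separate urgent class in the classifier, and a mark in the ABP document showing that a query was discussed, are optional.

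The cost is one short text to approve and translate per language, and one log count. The sample size does not change. The message assesses nothing, so it stays within the role of a communication tool. The downside is that it will often appear when it is not needed. The app is not yet built, so the change is cheapest now.
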